### 2.5. Statistical Analysis

**Sample size calculation.** Assuming 20% prevalence in source population, and based on a one-sided hypothesis, 100 patients will be included in each strategy arm to demonstrate a 15% difference between each strategy with statistical risks at 5% (type I error, α) and 15% (type II error, β). We are planning to enroll 1000 patients to consider a maximum patient loss of 10%. Considering that each investigator involved in the HepyPrim study follows more than 1200 patients each year, the inclusion objective was set to 50 patients per investigator and the number of investigators was set to 20. These investigators have been selected in the newly constituted “physicians’ network for research in New Aquitaine”.

**Analysis.** The data will be analyzed blindly on an intention-to-treat basis, assuming a non-inferiority hypothesis. No interim analysis is planned. A per protocol analysis will be performed as a secondary sensitivity analysis. Quantitative variables will be described by their mean and standard deviation or median and interquartile range according to the normality of the distribution. Categorical variables will be described by their number and percentage. Continuous variables will be compared by a Student’s *t*-test or Mann–Whitney U-test according to the normality of the distribution. Categorical variables will be compared by a chi-square test or Fisher’s exact test. The tests will be analyzed using GraphPad Prism version 9.0 (GraphPad Software, San Diego, CA, USA). A significant difference will be retained for a *p*-value < 0.05. All tests will be two-tailed, stratified by center and for multiple comparisons if appropriate.

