**Figure 2 jcm-11-01151-f002:**
[figure not shown]
CONSORT Flow chart of the HepyPrim Study. X: data could not be predicted before the beginning of the screening. Y (= y1 + y2 + y3 + y4), corresponding to patients lost to follow-up, will be less than 50 patients per allocation group.

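### The planned 1000 patients contain no allowance for the stated 10% loss: at 20% prevalence they give exactly the 100 infected per arm that the power claim needs

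*Protocol article*

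**What the plan says.** Section 2.5 of the protocol article, under the sample size calculation, opens with "Assuming 20% prevalence in source population" and continues, "based on a one-sided hypothesis", that "100 patients will be included in each strategy arm to demonstrate a 15% difference between each strategy". The type I error is 5% and the type II error 15%. The next sentence gives the total: "We are planning to enroll 1000 patients to consider a maximum patient loss of 10" per cent. The total is then built up a second way: "the inclusion objective was set to 50 patients per investigator and the number of investigators was set to 20".

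The legend of Figure 2 repeats the loss assumption by arm. Y, "corresponding to patients lost to follow-up, will be less than 50 patients per allocation group". With 1:1 allocation (section 2.1) there are 500 per arm, so 50 is 10% of those randomised.

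The primary endpoint (section 2.3) is cure, shown by a urea breath test after the end of treatment. Under section 2.1, only patients found infected and then treated come to that test.

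**The concern.** The paragraph gives the 10% loss as the reason for enrolling 1000. The only other input that leads from 100 per arm to 1000 in total is the 20% prevalence, and that step alone already gives 1000. If so, the allowance is claimed but not present.

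The error rates are attached to the 100 per arm. If some of those 100 have no breath test, the comparison rests on fewer patients than the number that carries the 85% power. For a non-inferiority question this means a larger chance of failing to show non-inferiority when it is true.

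The loss is also expressed on all randomised patients. About 400 of the 500 per arm are expected to be uninfected and have no post-treatment breath test to miss. A loss figure for the 500 therefore does not say how many of the roughly 100 who supply the endpoint may be missing.

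**Working it through.** **Inputs.** From section 2.5: 100 per arm, 15-point difference, one-sided 5%, power 85%, prevalence 20%, 1000 enrolled, maximum loss 10%. From section 2.1: 1:1 allocation. Not stated: the cure rate.

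**1. Reproduce the 1000.**
- Without loss: 2 x 100 / 0.20 = 1000. This matches exactly.
- Site target: 20 x 50 = 1000. The total is therefore not a misprint.
- With 10% loss: 100 / (0.90 x 0.20) = 555.6, so 556 per arm and 1112 in total.
- Variants: rounding the infected up to 112 per arm first gives 2 x 112 / 0.20 = 1120. The cruder n x 1.10 gives 2 x 110 / 0.20 = 1100.

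Only a loss of zero reproduces 1000.

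**2. Evaluable infected patients at the maximum loss.** 1000 x 0.20 x 0.90 / 2 = 90 per arm, if loss is the same among infected and uninfected patients.

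**3. Reproduce the 100.** For non-inferiority with a common cure rate p, n per arm = 2p(1-p)(1.645 + 1.036)² / 0.15². This gives 103 at p = 0.80, 100 at p = 0.806 and 99 at p = 0.81. The 100 is consistent with an unstated cure rate of about 80 to 81%.

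**4. Power at 90 per arm, taking the plan's 85% at 100 as given.** No cure rate is needed, because the standardised difference scales with the square root of n:
- 90 per arm: Phi(2.681 x sqrt(0.90) - 1.645) = Phi(0.899) = 81.6%
- 95 per arm (5% loss): Phi(2.681 x sqrt(0.95) - 1.645) = Phi(0.968) = about 83%

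**5. Power for assumed cure rates**, from Phi(0.15 / sqrt(2p(1-p)/n) - 1.645):

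| Assumed cure rate | n = 100 | n = 90 |
|---|---|---|
| 80% | 84.3% | 80.8% |
| 80.6% | 85.0% | 81.6% |
| 81% | 85.5% | 82.1% |
| 83% | 88.1% | 84.9% |

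Over the cure rates that reproduce the plan's 100 (80 to 81%), 90 per arm gives about 81 to 82%. The 83% row bears on the first objection.

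**The case against.** Three readings could rescue the plan.

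- **The 100 already includes the loss.** Inclusion can mean enrolment, in which case 90 would be the number needed. That fits an assumed cure rate of about 83% (n = 91), only two to three points above the rate that fits 100. It cannot be excluded by arithmetic, since no cure rate is printed. The text does not say it, however: it attaches the error rates to the 100 and the loss to the 1000.
- **Intention-to-treat keeps lost patients in the denominator.** If they were counted as failures, 100 per arm would be analysed. The article does not say how they are handled, and the 1000 would still contain no allowance.
- **Prevalence may exceed 20%.** The introduction gives 20 to 30% for France, and the trial enrols patients with an indication for testing. About 22.2% would leave 100 per arm after 10% loss (1000 x 0.222 x 0.90 / 2 = 99.9). This makes the consequence less likely but does not repair the calculation, which assumes 20%.

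Three stronger readings are tempting and not supported.

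- A reader might infer that the trial will end with 90 per arm. The 10% is a maximum, and the Figure 2 legend says fewer than 50, so 90 is the figure at the upper limit only.
- A reader might infer from that legend that half of the infected patients could be lost within a permitted limit. The legend is a forecast, not a rule. Patients can also be lost before diagnosis, and nothing suggests that all losses would fall among the infected.
- A reader might object that the number infected varies by chance and may fall below 100. That is true of any plan sized on an expected count and is not an error here.

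**Conclusion.** The point holds as an arithmetic error in the printed justification. At the assumed 20% prevalence, 1000 patients yield exactly 100 infected per arm, so the 10% loss allowance given as the reason for the 1000 is not in it. This follows from the article's own inputs and needs no assumption about the cure rate.

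The consequence is modest and conditional. At the maximum 10% loss, spread evenly, about 90 evaluable infected patients per arm remain. Power is then about 82% if 100 per arm gives the stated 85%, or about 81 to 82% for assumed cure rates of 80 to 81%. The type II error becomes about 18 to 19% instead of 15%. Smaller losses cost less: about 83% power at 5% loss. The figures rest on the 100 being evaluable patients, which is the natural reading because the error rates are attached to that number. The documents do not support a claim of serious loss of power.

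**What to change.** Correct the sample size paragraph in one of two ways.

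- **Keep 1000.** State that at 20% prevalence it gives 100 infected patients per arm before loss and about 90 after 10% loss, with power of about 81 to 82% at the stated difference and one-sided 5%. Cost: one sentence, and a stated power 3 to 4 points lower.
- **Keep 100 evaluable per arm after 10% loss.** State that about 1112 patients would be needed. Cost: 112 more patients, or about 56 per investigator (1112 / 20 = 55.6) instead of 50.

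In either case, state the loss allowance for the infected patients who supply the breath-test endpoint, and not only as 10% of the 500 randomised per arm. Give the cure rate behind the 100 as well, so that the power figure can be checked. If the 100 was meant to include losses already, say so and give the cure rate at which 90 suffices.

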The main objective of this study will be to evaluate, in a real-life situation, the feasibility of a strategy for the management of Hp infection by a non-invasive procedure in primary care and its non-inferiority in eradication rate compared with the strategy recommended by the HAS using a combination of serology and endoscopy. The secondary objectives of this study will be: to evaluate the adherence of patients to the care pathway (compliance to endoscopy, treatment, stool collection, serology); to evaluate the follow-up of recommendations in the management of Hp infections by health professionals (GPs and gastroenterologists) (e.g., empirical/guided treatment, evaluation of pre-neoplastic lesions); to validate, in real-life circumstances, real-time PCR in stool in comparison with serology in primary diagnosis and with urea breath test in eradication control.

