### 2.3. Study Outcomes

**Primary endpoint.** The primary endpoint will be an assessment of the cure rate through the results of a urea breath test performed 6 weeks after the end of treatment (proof of Hp eradication).

**Secondary endpoints.** The secondary endpoints will be assessment of: (i) the number of guided treatments (depending on the real-life application of the French authorities recommendations); (ii) the number of endoscopies (estimating the number of endoscopies avoided due to the optimized process); (iii) the number of biopsies at endoscopy; (iv) the number of patients who refused endoscopy after serology or positive PCR or did not follow-up after referral to the gastroenterologist; (v) the number of treatment side-effects and treatment dropouts; (vi) the discordance rate between real-time PCR tests in stool and serology in primary diagnosis; (vii) the discordance rate between real-time PCR tests in stool/breathing test in eradication control; and (viii) cure rate assessed by the result of a urea breath test performed 6 weeks after the end of treatment (proof of Hp eradication) depending on the antibiotic susceptibility testing identified at diagnostic.

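### Section 2.5 contradicts itself on the primary analysis: a one-sided non-inferiority premise, but the only rule printed for a binary endpoint is a two-tailed test for a difference

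*Protocol article*

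**What the plan says.** The Introduction makes non-inferiority part of the main objective: "its non-inferiority in eradication rate compared with the strategy recommended by the HAS using a combination of serology and endoscopy". Section 2.3 says how this is judged once therapy is complete: "The primary endpoint will be an assessment of the cure rate through the results of a urea breath test performed 6 weeks after the end" […]. Section 2.1 counts a negative breath test as success and a positive one as failure, so the outcome is binary.

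Section 2.5 then gives two sets of statements.

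- **Sample size:** The size is "based on a one-sided hypothesis, 100 patients will be included in each strategy arm". Its stated purpose is "to demonstrate a 15% difference between each strategy". The type I error is 5% and the type II error 15%. The assumed prevalence is 20%, planned enrolment is 1000, and the allowance for loss is 10%.
- **Analysis:** The opening statement is "The data will be analyzed blindly on an intention-to-treat basis, assuming a non-inferiority hypothesis". Further on, the rule for binary data is "Categorical variables will be compared by a chi-square test", and Fisher's exact test is the alternative. A significant difference is declared at p < 0.05, and every test is two-tailed and stratified by centre. The primary endpoint is not exempted.

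**The concern.** A chi-square or Fisher test takes equal cure rates as its null hypothesis. A non-inferiority analysis takes as its null that the new strategy is worse by at least a margin. A p-value from the first does not answer the second, in either direction: a non-significant result does not exclude a large deficit, and a significant result against the new arm can still lie inside a margin.

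The text leaves three things unreconciled: the hypothesis (non-inferiority or difference), the sidedness (one-sided for sizing, two-tailed for analysis), and the role of the 15% (margin or effect to be shown). Incompatible decision rules could each be defended from the same paragraph after the results are known, and the main conclusion of the trial depends on which is used.

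**Working it through.** **Inputs from section 2.5:** 15 points; one-sided α = 5% (z = 1.645); β = 15% (z = 1.036); 100 per arm. **Input from section 2.1:** 1:1 allocation. **Assumption:** the control cure rate is not stated, so 80%, 85% and 90% are used as a range.

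**1. Can the 100 per arm be reproduced?** Read as a non-inferiority margin with equal true cure rates p:

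n = (1.645 + 1.036)² × 2p(1 − p) / 0.15²

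| Assumed cure, both arms | n per arm |
|---|---|
| 75% | 120 |
| 80% | 7.19 × 0.32 / 0.0225 = 102.2 (103 rounded up) |
| 80.6% | 100 |
| 85% | 82 |
| 90% | 58 |

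The figure is reached if both rates are near 80%. It is also reached as a 15-point difference for several pairs:

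- 72.5% vs 87.5%, one-sided: 99
- 76% vs 91%, one-sided with continuity correction: 100
- 78% vs 93%, two-sided: 98
- 80% vs 95%, two-sided with continuity correction: 99

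So the sample size does not settle which meaning was intended.

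**2. What the printed test does when the new arm is 15 points worse.** Normal approximation at 80% vs 65%, n = 100:

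- Pooled rate 0.725; SE under equality = √(2 × 0.725 × 0.275 / 100) = 0.0631
- SE under the true rates = √[(0.80 × 0.20 + 0.65 × 0.35) / 100] = 0.0622
- P(non-significant) = Φ[(1.96 × 0.0631 − 0.15) / 0.0622] = Φ(−0.42), about 34%

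Exact binomial results for the uncorrected two-tailed chi-square test follow. The 90-per-arm column uses 1000 × 0.90 × 0.20 / 2 = 90, the number of infected patients per arm after 10% loss.

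| True cure, control vs new | Non-significant, 100 per arm | Non-significant, 90 per arm |
|---|---|---|
| 80% vs 65% | 33.4% | 37.9% |
| 85% vs 70% | 27% | 32% |
| 90% vs 75% | 18% | 23% |

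A one-sided 5% Wald bound compared with −15 points makes the false claim in about 5% of trials in the same settings.

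**3. The opposite reading.** If p < 0.05 in favour of the new arm were required, and both arms were at 80% with 100 per arm, the claim would succeed in 2.6% of trials. The rule based on a one-sided 5% bound succeeds in 84.5%.

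**4. Two worked tables, 100 per arm.**

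- Control 80 cured, new 70 cured: chi-square p = 0.10 (Fisher 0.14), so no significant difference. The 95% CI for new minus control is −21.9 to +1.9 points, which does not exclude a 15-point deficit.
- Control 99 cured, new 91 cured: chi-square p = 0.009 (Fisher 0.018), so a significant difference. The 95% CI is −13.9 to −2.1 points, which lies inside a 15-point margin.

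**5. Effect of the sidedness conflict on power.** At 80% in both arms and 100 per arm, SE = √(2 × 0.80 × 0.20 / 100) = 0.0566 and 0.15 / 0.0566 = 2.652.

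- One-sided 5% bound (90% CI): Φ(2.652 − 1.645) = 84.3% (84.5% exact)
- One-sided 2.5% bound (95% CI, matching two-tailed 0.05): Φ(2.652 − 1.960) = 75.5% (75.6% exact)

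**The case against.** A reader might infer that the plan definitively prescribes the wrong primary test, so that the trial cannot establish non-inferiority. The document does not support that. The chi-square sentence stands in a general paragraph on variable types and never names the cure rate, and the same paragraph opens with the non-inferiority hypothesis. It can be read as standard text for the other comparisons, with the primary method left open. The same data could also support non-inferiority once a bound is compared with a declared margin. This part of the objection stands, and it limits the point to a contradiction in the text.

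A condensed article may also leave the interval method and the exact decision rule to the full protocol or SAP. Their absence therefore carries no weight here. What remains is in print: a one-sided premise against all tests two-tailed, and non-inferiority against a rule for declaring a difference, with no exception for the primary endpoint. A SAP that followed this text would inherit the conflict.

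Two further inferences go too far. The article never says that p > 0.05 will be read as non-inferior, nor that p < 0.05 in favour of the new arm is required, so the error and success rates in steps 2 and 3 are conditional on those readings. And the fit to 100 per arm does not prove that 15% is the margin, or that 80% was assumed, because other readings also reach about 100.

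**Conclusion.** The point holds as a contradiction within section 2.5, and it needs to be resolved before the analysis because the primary conclusion depends on it. Applied as written to the cure rate, the two-tailed chi-square or Fisher test does not assess non-inferiority.

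If non-significance were taken as non-inferiority, the false-claim risk for a strategy 15 points worse would be about 18–33% at 100 per arm and 23–38% at 90 per arm, against the stated 5%. This rests on an assumed control cure rate of 80–90%, on 15 points being the relevant deficit, and on that reading of a non-significant result. Separately, the unresolved sidedness leaves power at either about 85% or about 76%, for 100 per arm and an assumed 80% cure in both arms.

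**What to change.** - State that the primary analysis compares the lower confidence bound for the difference in cure rates (intervention minus control, stratified by centre as already planned) with a declared non-inferiority margin.
- Have the sponsor confirm whether 15 points is that margin, and state the assumed cure rate. Neither should be filled in by back-calculation from the 100 per arm.
- Reconcile the one-sided 5% used for sizing with the statement that all tests are two-tailed, and restate power for the level chosen. A one-sided 5% bound corresponds to a 90% CI; two-tailed 0.05 points to a 95% CI.
- Limit the two-tailed chi-square/Fisher rule to the other comparisons.

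The cost is about one paragraph, with no new data or procedures. The downside is that the margin, the assumed rate and possibly a lower power become explicit and open to challenge.

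### Section 2.5 contradicts itself on the primary test's error rate: it is sized at one-sided 5%, but all tests are then declared two-tailed at 0.05, with no exception for non-inferiority.

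*Protocol article*

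**What the plan says.** Section 2.5 of the protocol article sets the error rate in two places.

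- **Sample size calculation.** The trial is sized "based on a one-sided hypothesis, 100 patients will be included in each strategy arm". Type I error is put at 5% and type II error at 15%, for a difference of 15% in the primary comparison. That is one-sided 5% and 85% power.
- **Analysis.** The data are to be analysed by intention to treat under a non-inferiority hypothesis, and significance is set at p below 0.05. After naming Student's t, Mann–Whitney, chi-square and Fisher's exact tests, the paragraph ends: "All tests will be two-tailed, stratified by center and for multiple comparisons if appropriate".

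The Introduction makes non-inferiority in eradication rate part of the main objective, and section 2.3 makes the cure rate on urea breath test the primary endpoint. The article names no confidence level and no specific non-inferiority test, and it does not exempt the primary comparison from the two-tailed rule.

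**The concern.** A one-sided 5% non-inferiority test corresponds to the lower limit of a two-sided 90% interval. A two-tailed rule at 0.05, applied to the same comparison, corresponds to the lower limit of a 95% interval and leaves 2.5% in the direction that matters. The two paragraphs therefore describe different tests for the comparison that decides the trial, and the stated type I and type II errors fit only one of them.

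Two things are at stake. The chance of missing true non-inferiority is 15% on one reading and about 24% on the other. There is also a band of observed results for which the two readings give opposite conclusions.

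**Working it through.** **Inputs, all from section 2.5 unless marked.** Type I error 5%, one-sided. Type II error 15%. Difference 15%, read here as a 15-point margin (the article does not call it a margin). 100 patients per arm, taken as infected and evaluable, which agrees with 1000 × 0.20 / 2 = 100. Normal quantiles: z(0.95) = 1.645, z(0.975) = 1.960, z(0.85) = 1.036. The expected cure rate is not stated, so it is **assumed** wherever it appears below.

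**1. The plan's own figure.** With equal true cure rates p in both arms, the non-inferiority formula is

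n per arm = (1.645 + 1.036)² × 2p(1 − p) / 0.15².

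At an assumed p = 0.80 this gives 7.19 × 0.32 / 0.0225, rounded up to 103. A result of exactly 100 needs p of about 0.806. A superiority reading also comes close for some pairs of rates: 72% against 87% gives 103. So 100 per arm is plausible at one-sided 5%, but it cannot be reproduced from the article's inputs alone.

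**2. Effect of the two-tailed rule, without a cure rate.** If 100 per arm gives 85% power at one-sided 5%, the standardised margin is 1.645 + 1.036 = 2.681. With 2.5% in the relevant tail:

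power = Phi(2.681 − 1.960) = Phi(0.721) = 0.765, about 76%.

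The size needed to keep 85% is 100 × (1.960 + 1.036)² / (1.645 + 1.036)² = 100 × 1.249, about 125 per arm.

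**3. Sensitivity to the missing cure rate.** Power = Phi(0.15 / SE − z), with SE = √(2p(1 − p)/100):

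| Assumed cure rate, both arms | Power, one-sided 5% | Power, one-sided 2.5% |
|---|---|---|
| 75% | 0.7895 | 0.6878 |
| 80% | 0.8430 | 0.7554 |
| 85% | 0.9075 | 0.8439 |

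Power falls in every row, by about 6 to 10 points. The absolute level depends on a rate that the article does not give.

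**4. Where the two readings disagree (illustration at the assumed 80%).** SE = √(0.32/100) = 0.0566. The half-width is 1.645 × 0.0566 = 9.3 points for the 90% interval and 1.960 × 0.0566 = 11.1 points for the 95% interval. An observed difference (new strategy minus reference) between about −5.7 points (9.3 − 15) and −3.9 points (11.1 − 15) clears a 15-point margin on the first interval and fails on the second. With equal true rates, the chance of landing there is 0.8430 − 0.7554 = 0.088, about 9%.

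**The case against.** The strongest reply is that the two-tailed sentence was never meant for the primary test. It closes a run of difference tests and follows the rule for declaring a significant difference, which a non-inferiority conclusion is not. On that reading it is generic wording for descriptive and secondary comparisons, and the primary test keeps the one-sided 5% on which it was sized. This is plausible, and it is why the 76% must stay conditional. It does not remove the contradiction: the sentence says all tests, and no exception is written.

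Three further points stand in part.

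- The literal two-tailed reading is the stricter one, so it does not inflate the type I error. The cost is in power and clarity.
- The article gives neither a confidence level nor an expected cure rate. The 90% and 95% intervals are translations of the two levels, and any absolute power figure rests on an assumption. At 85% cure, the stricter test would nearly keep the stated power.
- This is a condensed article. A full protocol or analysis plan may settle the level, so a reader should not infer that the choice will in fact be made after the results are known. What can be said is that the article fixes the level twice, in incompatible ways.

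**Conclusion.** The point holds as a contradiction within section 2.5 that needs correcting: the error rate of the deciding comparison is stated in two ways that cannot both apply. Its size is a fall from 85% to about 76% power, or a rise from 100 to about 125 evaluable patients per arm to prevent it. This rests on two conditions: that the stated 85% at one-sided 5% is right, and that the two-tailed rule governs the primary test.

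A reader might infer that the trial simply has 76% power, or that the primary test is sure to be run at the stricter level. The article supports neither. The first needs a cure rate that is not stated; over assumed rates of 75% to 85%, power at the stricter level runs from about 69% to 84%. The second needs the two-tailed sentence to override the one-sided hypothesis, and the text leaves that open. A one-sided 5% level is not itself the fault. The fault is that the powered test and the declared test differ.

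**What to change.** Before data are seen, state one level and sidedness for the primary non-inferiority comparison, in the same terms in both paragraphs of section 2.5. Either option resolves the contradiction:

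1. Keep the two-tailed rule for every test, judge non-inferiority on the two-sided 95% interval, and restate power at 100 evaluable patients per arm as about 76%.
2. Write that the primary non-inferiority test is the single exception to the two-tailed rule (one-sided 5%, two-sided 90% interval), keep the 85% figure, and report the 95% interval beside it.

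In both cases, give the expected cure rate behind the calculation and say whether the 15% is the non-inferiority margin, so that the power can be checked.

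The cost is about one sentence in each paragraph. The first option also means a less favourable stated power. Neither needs more patients. Only a wish to keep 85% under the first option would: about 125 evaluable per arm, or 2 × 125 / 0.20 = 1250 enrolled instead of 2 × 100 / 0.20 = 1000, before any allowance for loss.
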